## Abstract

**Background:**

Variability analysis of peak expiratory flow (PEF) and forced expiratory volume at 1 second (FEV1) has been used in research to predict exacerbations in adults with asthma. However, there is a paucity of data regarding PEF and FEV1 variability in healthy children and adolescents and those with asthma.

**Objective:**

The objective of this study is the assessment of PEF and FEV1 variability in (1) healthy children and adolescents, to define the normal daily fluctuation of PEF and FEV1 and the parameters that may influence it, and (2) children and adolescents with asthma, to explore the differences from healthy subjects and reveal any specific variability changes prior to exacerbation.

**Methods:**

The study will include 100 healthy children and adolescents aged 6-18 years (assessment of normal PEF and FEV1 variability) and 100 children and adolescents of the same age with diagnosed asthma (assessment of PEF and FEV1 variability in subjects with asthma). PEF and FEV1 measurements will be performed using an ultraportable spirometer (Spirobank Smart; MIR Medical International Research) capable of smartphone connection. Measurements will be performed twice a day between 7 AM and 9 AM and between 7 PM and 9 PM and will be dispatched via email to a central database for a period of 3 months. PEF and FEV1 variability will be assessed by detrended fluctuation and sample entropy analysis, aiming to define the normal pattern (healthy controls) and to detect and quantify any deviations among individuals with asthma. The anticipated duration of the study is 24 months.

**Results:**

The study is funded by the “C. Caratheodory” Programme of the University of Patras, Greece (PN 47014/24.9.2018). It was approved by the Ethics Committee (decision 218/19-03-2019) and the Scientific Board (decision 329/02-04-2019) of the University Hospital of Patras, Greece. Patient recruitment started in January 2020, and as of June 2020, 100 healthy children have been enrolled (74 of them have completed the measurements). The anticipated duration of the study is 24 months. The first part of the study (assessment of lung function variability in healthy children and adolescents) will be completed in August 2020, and the results will be available for publication by October 2020.

**Conclusions:**

Healthy children and adolescents may present normal short- and long-term fluctuations in lung function; the pattern of this variability may be influenced by age, sex, and environmental conditions. Significant lung function variability may also be present in children and adolescents with asthma, but the patterns may differ from those observed in healthy children and adolescents. Such data would improve our understanding regarding the chronobiology of asthma and permit the development of integrated tools for assessing the level of control and risk of future exacerbations.

**Trial Registration:**

ClinicalTrials.gov NCT04163146; https://clinicaltrials.gov/ct2/show/NCT04163146

**International Registered Report Identifier (IRRID):**

DERR1-10.2196/20350

## Introduction

Asthma is the most common chronic disease of childhood and represents an important cause of morbidity worldwide [1]. The disease is characterized by episodes of reversible airway obstruction (exacerbations), with specific symptoms (such as wheezing, dyspnea, coughing, chest tightness) and a decrease in peak expiratory flow (PEF) and forced expiratory volume at 1 second (FEV1) [2]_._ However, lung function changes occur in parallel with clinical deterioration, thus presenting limited ability to predict the exacerbation of the disease [3].

Both PEF and FEV1 demonstrate significant daily variability, in relation to circadian and day-by-day fluctuation of measured values [4,5]. In healthy individuals, the pattern of these fluctuations remains constant over long time periods (weeks or months); this contrasts with patients with asthma, for whom PEF and FEV1 variability increase with loss of disease control, especially prior to exacerbations [5,6]. Thus, lung function variability analysis has been used in research to recognize high-risk patients, predict asthma exacerbations, and evaluate the effectiveness of treatment [6-10].

In clinical practice, however, the evaluation of lung function variability requires daily measurements with portable devices, the recording of PEF and FEV1 values in specialized diaries, and periodic evaluations of the data by the attending physicians [2]. The whole process may be both complicated and time-consuming, reducing patients’ adherence—especially in the cases of children and adolescents [11,12]. In addition, the periodic post hoc review of measurements may hamper the prediction of exacerbations, as the time of evaluation may not coincide with changes in the variability of lung function that characterize the loss of asthma control [12].

In recent years, technological advancements in the field of biosensors and microprocessors have permitted the development of reliable, low-cost, ultraportable spirometers, able to connect with cutting-edge mobile phones (smartphones) and monitor lung function parameters in real time and from a distance [13]. The introduction of such devices in clinical practice may overcome most of the aforementioned barriers in following up lung function parameters in the long term [13].

Currently, there is a paucity of data regarding long-term PEF and FEV1 variability in children and adolescents; this holds particularly true for children and adolescents with asthma. Such data would improve our understanding regarding the chronobiological aspects of the disease and may permit the development of integrated tools for assessing the level of asthma control and the risk of future exacerbations.

## Methods

### Study Objectives and Hypotheses

The first objective of the study (objective 1) is the assessment of lung function variability in healthy children and adolescents, focusing on the range and pattern of short- and long-term fluctuations of PEF and FEV1 and the parameters that may influence them. The second objective (objective 2) is the assessment of lung function variability in children and adolescents with asthma; the pattern of short- and long-term PEF and FEV_1_ variability will be established and the differences from healthy subjects will be defined. Specific changes in the variability pattern prior to exacerbation will also be sought and described (objective 3).

We hypothesize that healthy children and adolescents present normal short- and long-term variability of PEF and FEV1, and that the pattern of variability is influenced by age, sex, and environmental stimuli (season, weather conditions, viral infections, etc). Significant lung function variability is also expected for children and adolescents with asthma; the patterns of variability in children and adolescents with asthma may differ from those observed in healthy children and adolescents, being also influenced by environmental conditions and treatment modalities (controller therapy) in a distinguishable way. Finally, we hypothesize that changes in the pattern of lung function variability occur prior to the loss of asthma control and, thus, may be used to predict the exacerbations of the disease.

### Study Design

The study was designed as a nonrandomized, open-label, interventional clinical trial with single group assignment (2 study groups).

### Study Population

The study will include a cohort of healthy children and adolescents (n=100) for the assessment of normal PEF and FEV1 variability (objective 1) and a cohort of children and adolescents with asthma (n=100) for the assessment of PEF and FEV1 variability in this population (objective 2), as well as an investigation of its potential clinical relevance (objective 3). Participants will be recruited at the Pediatric Respiratory Unit and the Department of Pediatrics of the University Hospital of Patras, and at private pediatric offices in the city of Thessaloniki, Korinth, and Trikala, Greece. Each participant will receive a unique study number (comprising 2 letters and 8 numbers in random order).

### Sample Size Estimation

Data regarding long-term PEF and FEV1 variability in children and adolescents (with or without asthma) are lacking. Based on lung function variability, data from adults with asthma [14], and assuming a maximum dropout rate of 10%, we estimated that a sample size of 200 children and adolescents (100 in each group) would allow us to detect a difference of at least 1% in PEF or FEV1 coefficient of variation (CV) between healthy participants and participants with asthma, with 90% power at the 0.05 level. Sample size estimation was performed using the G*Power software (version 3.1.6) [15] after assuming a nonparametric distribution of lung function parameters (Wilcoxon rank-sum test).

### Inclusion and Exclusion Criteria

Inclusion criteria for both cohorts are individuals 6-18 years old; who have access to (or whose parents have access to) a smartphone with internet connection (Wi-Fi or mobile data); and who have given (or whose parents have given) informed, written consent to participate.

Inclusion criteria for the cohort of healthy children and adolescents are no asthma diagnosis or prescription of relevant medication (beta-2 agonists, anticholinergics, inhaled corticosteroids or montelukast) in the last 2 years; and normal baseline spirometry, defined as FEV1 and FEV1/FVC > 80% of predicted (Global Lung Initiative [GLI] normative data [16]) without significant reversibility (FEV1 change < 10%) after administration of 300 μg salbutamol inhaler.

Inclusion criteria for the cohort of children and adolescents with asthma are doctor-diagnosed mild or moderate asthma [2] in the last 2 years; administration of controller therapy for at least 6 months in the previous year; and at least one spirometry, with FEV1 and FEV1/FVC < 80% of predicted (GLI normative data [16]) in the previous year.

Exclusion criteria for both cohorts are major disabilities (eg, chromosome abnormalities, neurological or muscular disorders, neurodevelopmental delay) that may hamper the proper performance of lung function measurements; respiratory conditions (eg, severe respiratory infection, chest trauma) or other health-related events (eg, surgery, trauma) in the month prior to enrollment or during the 3-month period of observation; failure to complete the run-in period successfully (ie, to perform acceptable spirometries at the predetermined time frames); or inability to perform 3 consecutive measurements or 6 measurements in total (3.3% of the anticipated 180 measurements) within the 3-month period of observation.

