### Protocol

Tests will be performed according to American Thoracic Society/European Respiratory Society (ATS/ERS) standards [18]. The technique will be demonstrated by one of the investigators at enrollment, while detailed information will also be available through the online video resources on the study web site [17]. Measurements will be performed twice a day between 7 AM and 9 AM and between 7 PM and 9 PM. Each participant must perform at least 3 technically acceptable maneuvers. Completed measurements will be dispatched by the participants or their parents to a central database via email (encrypted pdf format).

Eligible children and adolescents will initially be asked to complete a run-in period of 10 days (20 trials) to assess their ability to perform technically acceptable spirometries (daily and at predetermined time frames), dispatch the measurements to the central database, and comply to investigators instructions. Those who will demonstrate satisfactory adherence will proceed to the main study consisting of daily measurements at predetermined time frames for a period of 3 months (90 days, 180 trials).

The expected duration of the study is 24 months and it will include two phases: Phase I and Phase II. Phase I will proceed from January 2020 to September 2020 and will consist of assessments of lung function variability in healthy children and adolescents. Phase II will proceed from October 2020 to December 2021 and will consist of assessments of lung function variability in children and adolescents with asthma.

A flow chart of the study is presented in Figure 1. The protocol is in accordance with SPIRIT (standard protocol items: recommendations for interventional trials) guidelines (Figure 2).

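### The exclusion for respiratory conditions during observation has no exemption for asthma exacerbations, so it can exclude infection-related exacerbations that objective 3 sets out to study

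*Protocol article*

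**What the plan says.** The exclusion list in the Inclusion and Exclusion Criteria section of the protocol article opens with "Exclusion criteria for both cohorts are major disabilities", so every item in it applies to healthy children and to children with asthma. One item is "respiratory conditions (eg, severe respiratory infection, chest trauma) or other health-related events (eg, surgery, trauma) in the month prior to enrollment or during" the 3-month observation period. It therefore acts after enrolment as well as before. Another item in the list, also acting after enrolment, is "inability to perform 3 consecutive measurements or 6 measurements in total (3.3% of the anticipated 180 measurements".

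The Study Objectives and Hypotheses section states: "Specific changes in the variability pattern prior to exacerbation will also be sought and described (objective 3". The Study Population section assigns that objective to the asthma cohort. The hypotheses expect that "changes in the pattern of lung function variability occur prior to the loss of asthma control", and for healthy children that "the pattern of variability is influenced by age, sex, and environmental stimuli (season, weather conditions, viral infections, etc". For children with asthma, environmental conditions are also expected to influence the pattern.

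The main study runs "for a period of 3 months (90 days, 180 trials". Phase II, the asthma cohort, is scheduled to start in October 2020.

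**The concern.** In the asthma cohort the same event can be an outcome and a reason for exclusion. A respiratory infection that brings on an exacerbation is what objective 3 wants to look back from, but if the infection is severe the criterion excludes the child. Nothing in the article separates an exacerbation to be studied from a respiratory condition that excludes.

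This is selection on something that happens after enrolment and is related to the outcome. The Introduction says that variability rises as asthma control is lost, especially before exacerbations. Excluding children for events tied to loss of control would leave a more stable asthma cohort. At stake are the number of events available to objective 3, the asthma side of the comparison in objective 2, and the severe end of the infection effect in the hypotheses.

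**Working it through.** **1. Reading the criterion against objective 3.** The criterion gives examples rather than a closed list.

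- Narrow reading: of infections, only severe respiratory infection excludes. Exacerbations without one stay, and so do milder viral infections. Objective 3 loses only the exacerbations that come with a severe infection.
- Broad reading: any exacerbation is a respiratory condition. Objective 3 then has no eligible events.

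Both readings take events away from objective 3, and the text does not say which applies.

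**2. How many children objective 3 could lose.** The plan has "a sample size of 200 children and adolescents (100 in each group") and allows 10% dropout, so 100 × (1 − 0.10) = 90 evaluable children with asthma. The article gives no exacerbation rate and no share of exacerbations that would trigger the rule. Both are assumptions here.

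Children remaining = 90 × p × (1 − f), where p is the proportion with an exacerbation in 3 months and f is the share of those excluded.

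| f | p = 10% (9 children) | p = 40% (36 children) |
|---|---|---|
| 25% | 6.75 | 27 |
| 50% | 4.5 | 18 |
| 75% | 2.25 | 9 |
| 100% | 0 | 0 |

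**3. Direction of bias in the asthma cohort.** Let q = p × f be the fraction excluded, and Δ the excess of the excluded children's mean coefficient of variation (CV) over that of the retained children. The full-cohort mean is (1 − q) × retained mean + q × excluded mean, so the retained mean falls short of it by q × Δ. In the grid above q runs from 0.10 × 0.25 = 2.5% to 0.40 × 1.00 = 40%. The Introduction supports Δ > 0, but the article gives neither Δ nor q. The direction can be argued; the amount cannot be calculated.

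**4. Power for objective 2.** The plan's figure is 100 per group for a CV difference of 1%, with 90% power at the 0.05 level by the Wilcoxon rank-sum test. It cannot be reproduced because the SD is not stated. I solved for the SD it implies, taking 1% as one CV point, a two-sided test, 90 per group and relative efficiency 3/π = 0.955:

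SD = √(90 × 0.955 / 2) / (1.960 + 1.282) = 6.555 / 3.242 = 2.02 CV points.

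With 90 healthy children, power is Φ(1 / [SD × √((1/n₁ + 1/n₂)/0.955)] − 1.960):

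- 90 children with asthma: 90.0%
- 80: 88.2%
- 70: 85.8%

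The cost in power is modest. The harm lies in which children are lost.

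**5. The missed-measurement rule.** Three consecutive sessions at two per day is 1.5 days; 6/180 = 3.3%. A child too ill to blow for 1.5 days could be excluded by this rule even if the respiratory criterion were changed.

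**6. Shortened series.** The Variability Analysis section averages CV over 24 windows of 14 measurements, step 7. These need 14 + 23 × 7 = 175 of the 180 readings. A series stopped at onset has fewer windows, so keeping these children requires a stated rule for short series.

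**The case against.** The strongest reply is that the protocol should be read as a whole. It names severe infection, chest trauma, surgery and trauma, not exacerbations. The Introduction describes exacerbations separately, and objective 3 is about them, so the authors cannot have meant to exclude them. Milder infections stay in on any reading that keeps to the named examples. This stands against the claim that the rule removes all exacerbations or the whole infection effect, which a reader might infer. It does not help the child whose exacerbation comes with a severe respiratory infection: that child meets a named exclusion and has the event of interest.

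A second reply is that leaving severely ill children out of a reference range for normal variability is a legitimate choice. For objective 1 this stands. It does not carry over to the asthma cohort.

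Third, the same rule applies to both cohorts, so the net bias in the difference between them is not established. This also stands. The argument here concerns the asthma side only.

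Two further inferences are tempting. One is that all readings before the excluding event are discarded. The article does not say so; it is silent on whether they are kept. The other is that healthy children have already been removed in Phase I. The Results section reports 100 enrolled and 74 finished by June 2020, and the other 26 may still have been under observation.

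**Conclusion.** The concern holds in limited form. As written, the criterion reaches the asthma cohort during observation without exempting exacerbations. It can therefore exclude infection-related exacerbations and cuts off the severe end of the hypothesised infection effect. This is a conflict between stated passages, not a detail left to a fuller document.

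The loss to objective 3 is partial on the narrow reading and total only if every exacerbation counts as a respiratory condition. The counts above rest wholly on assumed rates; they show that the range is wide, not where the trial will fall in it. Objective 3 is descriptive and has no target number of events, so no threshold is missed. Variability in asthma would be expected to be understated, by an unknown amount. The power cost to objective 2 is small.

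**What to change.** Before Phase II starts, reconcile the objectives, the study population and the exclusion criteria:

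- **Asthma cohort.** Limit the respiratory-condition exclusion to the month before enrolment. Treat respiratory infections and exacerbations during observation as events with recorded dates, keep the child, and use all readings up to onset for objective 3.
- **Missed sessions.** State that sessions missed because of such an event do not remove the child under the rule of 3 consecutive or 6 in total. Without this, the first change can be undone by the second rule.
- **Objective 2.** Report the comparison with these children included. As a sensitivity analysis, repeat it with the ill period or these children left out. State how detrended fluctuation analysis, sample entropy and the moving-window CV handle gaps and shortened series.
- **Healthy cohort.** The exclusion may stay as the definition of the reference population. Add a sensitivity analysis that includes whatever readings are available from any excluded children.

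The cost is a revision of two criteria, the recording of event dates, the sensitivity analyses and a rule for incomplete series. No extra participants or lung function measurements are needed, and readings already enter the registry as they arrive. The downside is some incomplete and more heterogeneous series.

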### Ethics Approval and Consent to Participate

This study was approved by the Ethics Committee (decision 218/19-03-2019) and the Scientific Board (decision 329/02-04-2019) of the University Hospital of Patras, Greece. The study was registered with ClinicalTrials.gov under the number NCT04163146 (registered on November 14, 2019). Informed consent from parents, or from parents and participants (in the case of adolescents older than 12 years of age), will be obtained at inclusion. The informed consent grants access to the participants’ measurements and medical files, and permits the transmission of data through the internet, given that all conditions of anonymity and data protection are met.

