### Variability Analysis

Participant-specific files will be used for variability analysis, focusing primarily on the variability of PEF and FEV1 and secondarily on FEV1/FVC and FEF25-75. All variables will be transformed into percentage predicted values according to GLI normative data [16].

Lung function variability will be assessed in 3 ways: (1) standard variability indices, (2) detrended fluctuation analysis (DFA), and (3) sample entropy (SampEn).

Standard variability indices such as CV (defined as SD divided by the mean) will be used. To avoid any bias due to the presence of trends within the time series, CV will also be calculated as the average of 24 moving windows (length 14 measurements; step 7 measurements).

DFA is a method that has been widely used for the investigation of intrinsic correlation within time series [19]. Initially, the square root of the time series F(*n*) is calculated for segments of different (time) length *n*. A linear relationship in the logarithmic graph F(*n*) - log(*n*) indicates the existence of fractal architecture in the scaling of the specific data, while the slope *a* of the line describes the pattern of long-term fluctuations [19]. A change in daily variability of PEF or FEV1 results in a simultaneous deviation from the predetermined *a* value [6]. This deviation can easily be detected and quantified. It has been shown that the magnitude of *a* deviation reflects the likelihood of asthma exacerbation within the next month [6].

SampEn is a measure of increased irregularity or complexity, which relies on the identification of recurrent patterns within a nonstationary time series (ie, the probability that a series of points within the signal will repeat themselves at a subsequent time-point) [20]. Within a regular and less complex system, the frequency of sequence matches is high; therefore, the entropy is low. SampEn has emerged as a more reliable index of dynamic variability, mainly because it is relatively independent of the length of the time series [20].

Variability analysis will be performed in the MatLab environment.

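### The missed-measurement exclusion makes no exception for asthma exacerbations, so it can selectively remove children whose pre-event readings objective 3 needs

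*Protocol article*

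**What the plan says.** In the protocol article, the Inclusion and Exclusion Criteria list exclusions that apply to both cohorts. Two of them can be met after a child has entered the main study.

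- Missed sessions: "inability to perform 3 consecutive measurements or 6 measurements in total (3.3% of the anticipated 180 measurements) within the 3-month period of observation".
- Intercurrent illness: "respiratory conditions (eg, severe respiratory infection, chest trauma) or other health-related events (eg, surgery, trauma) in the month prior to enrollment or during" the three months of observation.

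The Protocol section sets two sessions a day for 90 days, 180 in all, after a 10-day run-in. Data Acquisition and Monitoring has the session table checked at 11 AM and 11 PM, with a telephone call when measurements are missing.

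Study Objectives and Hypotheses states the third aim: "Specific changes in the variability pattern prior to exacerbation will also be sought and described (objective 3"). Study Population assigns that aim to the asthma cohort. The Introduction says that in patients with asthma PEF and FEV1 "variability increase with loss of disease control, especially prior to exacerbations".

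Neither exclusion mentions an exacerbation, either to include it or to exempt it.

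**The concern.** The missed-session rule acts on something that happens during follow-up, and in the asthma cohort a plausible cause of a short gap is the very event that objective 3 studies. A child too unwell to blow for a day and a half is excluded, although the readings leading up to the event have already been sent in. A child with a milder episode who keeps blowing stays. Objective 3 would then describe a selected, probably milder, set of exacerbations.

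Objective 2 may also be affected. On the Introduction's own premise, the children removed would tend to have high variability, so the asthma cohort's average could come out too low.

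This is more than a detail left to an analysis plan. It is an explicit rule with numeric thresholds, and a later plan could soften it only by departing from it.

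**Working it through.** **1. The plan's own figures.** 90 days × 2 = 180 sessions. 6/180 = 3.33%, matching the stated 3.3%. Three consecutive sessions ÷ 2 per day = 1.5 days. The percentage gloss shows that the clause counts missed sessions. Read literally, at most five misses are tolerated, and never three in a row.

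**2. What one short gap does.** An exact recursion over 180 sessions tracks total misses and the current run of misses. A child is excluded at a run of 3 or a total of 6. Background misses are assumed independent at rate p (an assumption), and a gap of k forced misses is placed mid-series.

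| Background miss rate p | No gap | Gap of 2 sessions | Gap of 3 sessions |
|---|---|---|---|
| 1% | 1.0% | 11.9% | 100% |
| 1.5% | 5.6% | 29.4% | 100% |
| 2% | 15.4% | 49.0% | 100% |

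A gap of three sessions excludes with certainty, however good the child's adherence otherwise is. A one-day gap raises the risk about twelvefold at p = 1% (11.9/1.0) and about threefold at p = 2% (49.0/15.4).

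**3. Events lost to objective 3.** Let f be the share of the 100 children with asthma who exacerbate in three months, and e the share of those who miss three or more sessions in a row. The document gives neither; both are assumed. Children lost = 100 × f × e.

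- Low: 100 × 0.1 × 0.25 = 2.5 of 10
- Middle: 100 × 0.2 × 0.5 = 10 of 20
- High: 100 × 0.3 × 0.75 = 22.5 of 30

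**4. Shift in the asthma mean CV.** Let d be the excess CV, in points, of exacerbating over stable children with asthma (assumed). The mean excess is f·d with everyone kept, and d·f(1−e)/(1−f·e) after exclusion. The shift is the difference.

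- Low (d = 1): 0.100 − 0.077 = 0.02
- Middle (d = 2): 0.400 − 0.222 = 0.18
- High (d = 3): 0.900 − 0.290 = 0.61

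The study is sized for a difference of 1 point (Sample Size Estimation). These shifts concern the asthma mean alone. The same rule also removes healthy children, and the net effect on the difference cannot be worked out from the document.

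**5. Precision.** The SD behind the sample size is not stated. Working back from 90 evaluable children per group, 90% power, two-sided 0.05 and a Wilcoxon efficiency of 3/π gives an SD of 2.02. With 90 healthy children, losing 10%, 20% or 30% of the asthma cohort then leaves power at 90%, 88% or 86%. Selection is the problem here, more than loss of numbers.

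**The case against.** **Safeguards.** The run-in admits only children with satisfactory adherence, and sessions are checked twice a day with a call to the family. Three misses in a row would therefore usually follow at least one call. This stands as a limit on frequency: the assumed 25–75% takes no account of it, and how often the rule bites is unknown. But a call helps a family that forgot; it does not help a child who cannot blow, and it leaves the rule unchanged.

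**Purpose of the rule.** DFA and sample entropy work on ordered series, so near-complete data are a fair aim. That justifies a complete-series analysis set. It does not require discarding the child's earlier readings.

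A reader might infer more than the documents support:

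- *That the illness clause removes every exacerbating child.* Its examples are severe respiratory infection and chest trauma. It does not say whether an exacerbation counts, and reading it that way would empty objective 3. Only the missed-session clause is firm ground.
- *That the asthma-healthy difference is biased towards zero.* This is plausible, since exacerbations add losses only in the asthma cohort. It is not shown. Both cohorts are trimmed, and the hypotheses name "environmental stimuli (season, weather conditions, viral infections, etc") as influences on variability in healthy children too, so the healthy mean could also move.
- *That the asthma mean shifts by 0.61 points.* That sets all three assumed inputs at their extremes together, in a cohort limited to mild or moderate asthma with at least six months of controller therapy in the previous year.
- *That ordinary forgetfulness using up the 10% dropout allowance proves selection.* The no-gap column above describes random non-adherence, which is a separate feasibility question.

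**Conclusion.** The concern holds in a limited form. The missed-session rule has no exception for exacerbations and, as written, excludes a child with asthma who cannot measure for 1.5 days in one. That conflicts with objective 3, and the loss is selective rather than total, because children who keep blowing remain.

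The certain part is the rule itself: a three-session gap always excludes. The number of events lost (2.5 to 22.5, with 10 of 20 in the middle) rests on assumed rates of exacerbation and of missed sessions. For objective 2, understatement of asthma variability is possible. The middle figure of 0.18 points for the asthma mean is modest against the 1-point target, the low figure of 0.02 is negligible, and the net bias in the comparison is undetermined. The change is worth making before the asthma phase, mainly for the sake of objective 3.

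**What to change.** Amend the criteria before Phase II, which the Protocol section starts in October 2020.

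1. **Asthma cohort only.** Sessions missed because of an exacerbation do not count towards the limit of 3 consecutive or 6 in total. State that an exacerbation is not an excluding respiratory condition. Leave the illness and missed-session clauses unchanged for healthy children: lifting them there would bring children with severe infection, trauma or surgery into the series meant to define normal variability.
2. **Objective 3.** Date exacerbations from the medical files, to which consent already gives access (Ethics Approval and Consent to Participate). Analyse all readings up to onset, and require completeness only in a pre-onset window fixed in advance.
3. **Objective 2.** Keep these children. The plan says "CV will also be calculated as the average of 24 moving windows (length 14 measurements; step 7 measurements"). Compute CV from the readings available and keep the windows around the event. A threshold such as 12 of 14 readings would defeat the purpose: a window containing a whole three-session gap has 11, and with a step of 7 such a gap would normally delete one or two windows at the exacerbation. Run DFA and sample entropy on the available series, subject to a minimum length set in advance.
4. **Reporting.** Give the number of children who meet the present 3/6 rule, by cohort and reason, and repeat the main comparison under that rule as a sensitivity analysis.

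The cost is one amendment, a recorded reason for missed sessions and gap handling in the analysis scripts. No new spirometry or visits are needed. The drawback is that DFA is less stable on shorter or gapped series, which is why a minimum length and the sensitivity analysis are included.
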